### Power calculations

The following power calculations are based on effect sizes and CIs observed in our previously published results, which used data from 110 000 individuals prescribed either varenicline or nicotine replacement therapy.^13^ Based on the rate of 18 000 new prescriptions per year observed in the CPRD from 2006 to 2011,^13^ we estimate that with a further 4 years of follow-up the number of patients prescribed either varenicline or nicotine replacement therapy will have increased by 72 000. Therefore the total expected sample size for analysis will be around 180 000.

In our previous analysis using CPRD data the age-adjusted and sex-adjusted HR for self-harm/suicide for varenicline versus nicotine replacement therapy at 9 months was 0.73 (95% CI 0.54 to 0.99); after adjusting for possible confounders this became 0.90 (95% CI: 0.66 to 1.22).^13^ A 70% increase in sample size would lead to a reduction of the SE by a factor of 1.3, reducing the breadth of the above CI in the adjusted analysis from 0.56 to 0.43.

Rare outcomes, such as self-harm and suicide were used in previous analyses; in this project we will have greater power to explore more common outcome measures. For example, in the previous analysis the 9-month age-adjusted and sex-adjusted HR for all-cause mortality 9 months after first prescription for varenicline versus nicotine replacement therapy was 0.43 (95% CI 0.35 to 0.53); after controlling for possible confounders this became 0.49 (95% CI 0.40 to 0.61). A 70% increase in sample size would lead to a reduction of the SE by a factor of 1.3, reducing the breadth of the above CI in the adjusted analysis from 0.21 to 0.16.

For the effects of varenicline versus nicotine replacement therapy on all-cause mortality, instrumental variable analysis found a risk difference of 0.7 (95% CI −3.3 to 4.7) per 1000 patients treated after 9 months. We estimate that a 70% increase in sample size would narrow the CIs from 8.0 to 6.2.

Using data from our previous project, within 2 years of first prescription, we found 2517 admissions for respiratory disease among 1374 patients; 3144 admissions for cardiovascular disease among 1022 patients; and 3277 admissions for depression or anxiety among 213 patients. This is more events than we found for suicide and self-harm in our previous study; therefore we believe that there will be enough events for this analysis.

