### Data collection and linkage

We will use linked Hospital Episodes Statistics (HES) and ONS mortality data to define frequency of GP and hospital attendance, frequency of all-cause and cause-specific hospitalisation and all-cause and cause-specific mortality. We will test these hypotheses using data from GP practices linked to external data sets only.

These are important hard outcomes for our study. We have already established that for certain outcomes, such as cause specific mortality the linked ONS data are more accurate.^18^ While it is possible to investigate these outcomes using CPRD data from GPs, the data are less precise and consistently recorded.^18^ Thus analyses using linked data are likely to be more precise. Furthermore, the linked data provide direct evidence about secondary care attendance of patients via the HES data. Again, while there are some data about referrals to secondary care in the main tables of the CPRD, the data are not as comprehensive as HES data. Our outcomes of interest occur after September 2006; therefore, we believe that the linked HES and ONS data will provide sufficient coverage for these outcomes.

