#### Outcome measures

##### Outcome 1: Smoking abstinence

In the CPRD smoking status is indicated by whether the patient is a current, former or never smoker. As GPs are paid to record smoking status smoking behaviour is robustly recorded in the CPRD.^21^ Marston *et al*^21^ found that 84% of patients had smoking status recorded within a year of registering at a GP, and that smoking prevalence rates by age were similar in CPRD and the Health Survey of England. Booth *et al*^22^ found that the difference in prevalence of smoking estimate between the CPRD and the Health Survey for England was less than 1%, and the mean difference was 0.1% (95% CI −1.5% to 1.7%). Using unpublished data from CPRD sampled as part of the research reported in Thomas *et al*^13^ we found that 74% of patients prescribed smoking cessation medication had a subsequent record indicating smoking status. Of these 66% were indicated as current smokers and 33% as ex-smokers. We will initially define a patient as relapsed if they have any record indicating that the patient is a current smoker after their first prescription of a smoking cessation therapy. We will not be able to determine the smoking status of patients who do not return to the GP. Therefore, we will perform sensitivity analyses to examine whether the assumptions made about the smoking status of individuals who are not observed affect the results. For example, we will conduct a sensitivity analysis to see if the results are altered by assuming that patients with missing data have relapsed, or by assuming that patients with missing outcome data have achieved abstinence.

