#### Confounding factors

We will include gender, age in years at time of first prescription, previous psychiatric illness/consultation, previous use of psychotropic medications such as hypnotics, antipsychotics and antidepressants, previous self-harm, measures of alcohol consumption where appropriate mean/median number of GP visits per year, body mass index, SEP (deprivation score for area or residence) and major chronic illness (including: diabetes, cancer, arthritis) using the Charlson index.^26^
^27^ Relevant Read codes will be identified either by validated code lists or by searching for each of these events in the Read code dictionaries to identify any missing Read codes. Collider bias is a potential threat to the analysis; this type of bias occurs when the association between two variables changes on conditioning of a third variable if the third variable is affected by the first two variables. Collider bias could occur if we conditioned on events that happened as a result of the prescription the patient was issued. To prevent this bias from affecting our results, we will define each covariate using data inputted prior to the first prescription.^28^ If there are missing data in the covariates we will consider using multiple imputation.

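### The single covariate list omits prior hospital admissions, although mortality and hospitalisation are tested only in HES-linked practices and the quoted adjusted 9-month mortality HR of 0.49 suggests residual confounding by health status

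*Protocol article*

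**What the plan says.** The Confounding factors section gives one list of about ten items. Three are psychiatric: "previous psychiatric illness/consultation, previous use of psychotropic medications such as hypnotics, antipsychotics and antidepressants, previous self-harm". The others are gender, age, alcohol, GP visit rate, BMI, area deprivation and major chronic illness by the Charlson index. All covariates must be measured before the first prescription. Prior hospital admissions are not listed.

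The Statistical analysis section applies the methods to every outcome. Analysis 1 (Cox) adjusts for the whole list, and Analysis 2 (propensity score) is built on the same list.

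The Data collection and linkage section restricts the attendance, hospitalisation and mortality questions to linked practices and notes that "the linked data provide direct evidence about secondary care attendance of patients via the HES data".

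The Power calculations section quotes the investigators' previous study. The age- and sex-adjusted 9-month all-cause mortality HR "for varenicline versus nicotine replacement therapy was 0.43 (95% CI 0.35 to 0.53". The fuller adjustment is then reported in these words: "after controlling for possible confounders this became 0.49 (95% CI 0.40 to 0.61". For the same outcome, "instrumental variable analysis found a risk difference of 0.7" per 1000, with a 95% CI of −3.3 to 4.7. These figures are used only to project precision.

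**The concern.** If nicotine replacement tends to go to sicker smokers, varenicline will look protective against death and admission unless health status at prescription is well measured. A halving of deaths within 9 months is a large effect for a drug whose stated benefit is cessation, and it remained after adjustment. The article does not comment on its plausibility.

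Pre-index admissions are an obvious marker of recent serious illness. They come from a data set already linked for these outcomes, yet they are not used.

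The article's Strengths and limitations say that the three approaches rest on distinct assumptions. Analyses 1 and 2 do not differ on the assumption that matters here: both need no unmeasured confounding, and both use the same covariates. If health status is under-measured they will tend to agree for that reason. Bias of this kind does not shrink with sample size, so the larger cohort would narrow the interval around the same distorted value. The findings are meant to inform recommendations to two regulators.

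**Working it through.** **1. The plan's own precision figure.** The article states "A 70% increase in sample size would lead to a reduction of the SE by a factor of 1.3". Its projection for the mortality HR is worded as "reducing the breadth of the above CI in the adjusted analysis from 0.21 to 0.16". √1.7 = 1.304 and 0.21/1.304 = 0.161. With the article's counts, (110 000 + 72 000)/110 000 = 1.65, √1.65 = 1.29 and 0.21/1.29 = 0.163. Both round to 0.16, so the figure reproduces.

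On the log scale, SE = [ln 0.61 − ln 0.40]/3.92 = 0.108, and 0.108/1.304 = 0.083. The projected interval around an unchanged 0.49 is exp(−0.713 ± 1.96 × 0.083), about 0.42 to 0.58. The interval tightens whether or not 0.49 is causal.

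**2. How far adjustment moved the HR.** 1 − ln 0.49/ln 0.43 = 1 − 0.713/0.844 = 0.15. Adjustment removed about 15% of the log HR.

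**3. What quitting alone could produce.** Let a0 and a1 be abstinence on nicotine replacement and varenicline, and k the share of deaths that quitting removes within 9 months. Treating the HR as a risk ratio, and letting quitting act from day one (generous to the drug):

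HR = (1 − k·a1)/(1 − k·a0)

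The article gives neither k nor abstinence by drug, so these are assumptions. Its only anchor is pooled over both drugs: "Of these 66% were indicated as current smokers and 33% as ex-smokers", among the 74% with a later record. Counting patients without a record as smokers gives 0.74 × 0.33 = 24%.

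- k = 1, 30% v 40%: 0.60/0.70 = 0.86
- k = 0.5, 30% v 40%: 0.80/0.85 = 0.94

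| k | 30% v 40% | 20% v 40% | 25% v 50% | a1 needed for 0.49 if a0 = 0% | a1 needed for 0.49 if a0 = 25% |
|---|---|---|---|---|---|
| 1 | 0.86 | 0.75 | 0.67 | 51% | 63% |
| 0.75 | 0.90 | 0.82 | 0.77 | 68% | 80% |
| 0.5 | 0.94 | 0.89 | 0.86 | 102% | 114% |
| 0.3 | 0.97 | 0.94 | 0.92 | 170% | 182% |

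The last two columns use a1 = [1 − 0.49(1 − k·a0)]/k. At k = 0.5 or less, 0.49 is out of reach even if nobody on nicotine replacement quits. Above that it needs very large differences in abstinence. The upper limit, 0.61, at k = 0.5 needs 78% v 0% (0.39/0.5) or 93% v 25%.

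**4. Whether the instrumental variable result settles it.** An HR of 0.49 is roughly a 51% risk reduction. The lower limit of −3.3 per 1000 excludes that only if 9-month mortality on nicotine replacement exceeds 3.3/0.51 = 6.5 per 1000. The article does not give that rate.

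**The case against.** The strongest case against has five parts.

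- **The list is not narrow.** A reader might infer that it is mainly psychiatric and carried over from the self-harm study. Only three of about ten items are psychiatric; GP visits, BMI, deprivation, age, alcohol and Charlson all bear on physical health, and the article does not say where the list came from. This part stands.
- **The 0.49 comes from a study that cannot be seen here.** A reader might infer that this list left the bias in, so that the new Cox and matched analyses are bound to repeat it. The article does not name the confounders behind 0.49, so that is a risk and not a demonstrated outcome. This part stands.
- **The instrumental variable estimate might be read as contradicting the Cox result.** It does not: its interval spans zero and, by step 4, may still include a halving. This part stands.
- **The plan already handles confounding.** It admits unobserved confounding in general terms, and its instrumental variable analysis does not depend on this list being complete. That is real mitigation for the study as a whole, but it repairs neither Analysis 1 nor Analysis 2.
- **The remedy is unproven.** An unmeasured confounder would need risk-ratio associations of about 3.5 with both drug and death to explain 0.49 fully (E-value, with x = 1/0.49 = 2.04: 2.04 + √(2.04 × 1.04) = 3.5), or about 2.7 for the limit 0.61. Prior admissions may remove only part of any bias. That is a reason to pair them with a check, not to leave them out.

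**Conclusion.** The point holds in a limited form. The article fixes one covariate list for all outcomes, it contains no prior admissions, and mortality and hospitalisation are analysed only where HES is linked. An adjusted 9-month HR of 0.49 is hard to explain by quitting: assumed abstinence of 30% v 40% gives 0.86 at the extreme bound and 0.94 if quitting halves deaths. Residual confounding by health status is the natural reading, and Analyses 1 and 2 would share it.

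This rests on assumed abstinence by drug and an assumed short-term effect of quitting, and on quitting being the main beneficial route to survival. The aims also mention reports of less depression and anxiety, but give no size. Over the abstinence contrasts tabulated, no value of k brings the HR within 0.40 to 0.61; the nearest is 0.67, at 25% v 50% with quitting removing every death.

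A reader might extend the point to incident myocardial infarction and the other primary care diagnoses. The article defines those from CPRD Clinical and Referral files and states no linkage restriction for them, so the argument from linked data already in hand does not cover them.

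**What to change.** For the mortality and hospitalisation outcomes in linked practices:

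1. Add to both the Cox and the propensity models the numbers of all-cause, respiratory and cardiovascular HES admissions in the 12 months before the index prescription. This fits the plan's rule of using only pre-prescription data. First confirm that HES coverage reaches 12 months before the earliest index dates, which the article does not state.
2. Report the 0-3 month all-cause mortality HR from Analyses 1 and 2 as a check on residual confounding. An HR well below 1 that early, when quitting has had little time to act, should temper any claim of benefit. It is an aid to interpretation, not a pass/fail test.
3. State that agreement between Analyses 1 and 2 is not independent support, because both assume no unmeasured confounding and use the same covariates.

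The cost is a few extra covariates from a source already linked, one extra reported estimate and a sentence of interpretation. The covariates exist only in linked practices, where these outcomes are already analysed. Incident myocardial infarction and other CPRD-defined outcomes are outside this change; extending it to them would restrict their sample to linked practices.

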### Inclusion and exclusion criteria

We will include patients who were older than 18 and were prescribed medicines in British National Formulary (BNF) category 4.10.2 (Nicotine Dependence) from 1 September 2006, when varenicline was introduced to the UK, to the present. We will use patients prescribed other smoking cessation products (nicotine patches, gum, lozenges, and inhalers) as controls for patients prescribed varenicline. We will include patients whose records were classified as ‘acceptable’ by the CPRD from all ‘up to standard’ general practices (GPs) at least 18 months prior to date of entry of each cohort (1st March 2005). Up to standard GPs are practices that have submitted data that meets the CPRD quality control thresholds. Patient data are defined as ‘acceptable’ by the CPRD if they meet minimum quality control standards, for example their registration period with their GP is valid.

We will exclude patients who registered at a GP less than 365 days before the first recorded prescription, to allow for high-quality assessment of baseline data and possible confounders. Patients prescribed bupropion in the year before their index prescription of varenicline or nicotine replacement therapy will be excluded from the analysis. In the primary analysis we will exclude patients initially prescribed nicotine replacement therapies and varenicline together, although in our previous analysis this only occurred for 0.25% of all prescriptions.^13^

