##### Outcome 2: Frequency of GP and hospital attendance

We will define service use as the number of visits to GP and hospitals in the 3, 6, 9, 12, 24 and 48 months after first prescription. We will define GP appointments using the clinical data file of the CPRD. This includes all the diagnoses and symptoms that GPs record about all of their patients. As with the other outcomes, the vast majority of diagnoses and symptoms include the date on which the data were added to the database. We will use these dates to calculate the number of times each patient attends primary care. We will define the hospital visits outcome using the linked HES data. We will investigate all-cause hospitalisation and three specific causes of hospitalisation: (1) diseases of respiratory system (ICD-10=J00-J99), (2) cardiovascular disease (ICD-10=I00-I52) and (3) anxiety and depression (ICD-10=F31.3, F31.4, F31.5, F32, F40-F48). Causes of hospitalisation are available for approximately half of the sample. Again these data contain the date on which the event occurred, which we will use to define attendance to secondary care within 3, 6, 9, 12, 24 and 48 months after first prescription.

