##### Outcome 4: Incident respiratory illness, myocardial infarction, depression or anxiety

We will define the adverse event outcomes using the diagnosis records from the Clinical and Referral files in the CPRD. These files record all the diagnoses that the GPs input into their computer system. Each record in the table is given a diagnosis code based on the Read code categorisation. We will use validated Read code lists, for the three adverse event outcomes, respiratory illnesses, myocardial infarction or depression and anxiety, please see the cited papers for Read code lists.^23–25^ For eligible patients we will extract all records from the Clinical and Referral Tables that indicate the patient either received a specific diagnosis or were referred for a specific diagnosis. As with the therapy records for prescriptions described above, each Clinical and Referral Record indicates the date the information was inputted into the system. We will use this date to define the date that the diagnosis was performed. We will define a set of outcomes within 3, 6, 9, 12, 24 and 48 months after first prescription.

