#### Analysis 1: Conventional cox regression

In our first analysis, a conventional observational analysis, we will estimate HRs of the outcomes using Cox-proportional hazards models and the actual prescriptions issued to the patients.^29^ Each patient's date of entry into the cohort will be the date they were first prescribed a smoking cessation therapy. The date of exit for each outcome will be the date on which they first have an event, or are censored due to end of follow-up or death or leaving the practice. We will report these associations adjusted for basic confounders (age and gender), and results adjusted for all measured covariates described above.

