#### Analysis 2: Propensity score regression

In our second analysis we will construct a sample of patients balanced on covariates and risk factors using a propensity score.^30–33^ We will construct propensity scores using a logistic regression of the actual treatment received on the covariates described above. Therefore, each participant's propensity score will be their conditional probability (odds) of receiving varenicline versus nicotine replacement therapy. We will match each patient receiving varenicline to another patient receiving nicotine replacement therapy with the closest propensity score on a ratio of 1:1 using a nearest neighbour algorithm with no replacement, and matching will be restricted to the common support region. Patients outside the common support region are those prescribed varenicline with propensity scores higher than any patient prescribed nicotine replacement therapy and vice-versa. We will estimate HRs of the outcomes using the propensity score matched sample using Cox regressions using the same entry and exit information as the conventional Cox regression analysis described above.

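### Prior respiratory and cardiovascular disease has no covariate of its own, so the Cox and propensity score hazard ratios for those outcomes can keep avoidable confounding

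*Protocol article*

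**What the plan says.** The list in the protocol article under Confounding factors covers physical disease with a single item: "major chronic illness (including: diabetes, cancer, arthritis) using the Charlson index". Mental health history is listed in more detail: "previous psychiatric illness/consultation, previous use of psychotropic medications such as hypnotics, antipsychotics and antidepressants, previous self-harm". The other covariates are gender, age, alcohol, GP visit rate, body mass index and area deprivation. All are defined from data entered before the first prescription.

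The one list serves both analyses that report hazard ratios. Analysis 1 gives "results adjusted for all measured covariates described above"; Analysis 2 builds the score from a "logistic regression of the actual treatment received on the covariates described above". The Statistical analysis section applies both to every outcome.

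Those outcomes include hospital admissions grouped as "1) diseases of respiratory system (ICD-10=J00-J99), (2) cardiovascular disease (ICD-10=I00-I52", deaths in the same two groups (Outcome 3), and the diagnoses headed "Outcome 4: Incident respiratory illness, myocardial infarction, depression or anxiety". The inclusion and exclusion criteria remove nobody for earlier lung or heart disease. They concern such matters as registration time ("We will exclude patients who registered at a GP less than 365 days before the first recorded prescription"), bupropion in the preceding year, and a joint first prescription of both products.

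**The concern.** A patient's history of lung disease is likely to be among the strongest predictors of a later respiratory admission or death, and heart disease likewise for the cardiovascular outcomes. The covariate list gives neither its own term. There are two readings of the index item:

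- **The index contains these conditions.** A summed score treats a patient with lung disease like any other patient with the same total. If prescribers choose between varenicline and nicotine replacement differently for lung disease than for the other pooled conditions, patients with equal scores in the two groups carry different diseases. Adjusting for the score or matching on it does not correct that.
- **The index does not contain them.** The history is then not adjusted for, except through its correlation with age, GP visits and the other covariates.

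The Cox and matched analyses share the same list, so their agreement would not be independent support for the result. Balance on the score after matching could also hide imbalance on the disease that drives the outcome.

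**Working it through.** **The plan's own figures.** The documents give no figure for this confounding. The precision figures in Power calculations reproduce: dividing each interval width by √1.7 = 1.304 gives 0.56/1.304 = 0.43, 0.21/1.304 = 0.16 and 8.0/1.304 = 6.1, against the stated 0.43, 0.16 and 6.2.

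**Illustration: pooled reading.** No input here comes from the documents. Assume no drug effect, 30% on varenicline, and two independent conditions that each add one point to a score:

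- A, lung disease: prevalence 8–15%, rate ratio 3–6 for the respiratory outcome.
- B, another illness: prevalence 15–20%, rate ratio 1.0–1.2.
- Odds ratios of A and of B for receiving varenicline: each 0.6–1.2.

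One case by hand: A 12%, B 20%, rate ratios 5 and 1.1, odds ratios 0.6 (A) and 1.0 (B). Among patients with a score of 1, lung disease is the qualifying condition in 38.4% on nicotine replacement and 27.2% on varenicline. Relative rates in that stratum:

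- nicotine replacement: 0.384 × 5 + 0.616 × 1.1 = 2.60
- varenicline: 0.272 × 5 + 0.728 × 1.1 = 2.16
- ratio: 2.16/2.60 = 0.83, although the drug does nothing.

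The strata with scores 0 and 2 have a ratio of 1.00. Poisson regression on the expected counts, a rare-event stand-in for Cox regression, combines the strata:

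| Odds ratio A | Odds ratio B | Crude | Score-adjusted | A and B separate |
|---|---|---|---|---|
| 0.6 | 1.0 | 0.87 | 0.93 | 1.00 |
| 1.0 | 0.6 | 0.99 | 1.08 | 1.00 |
| 0.6 | 0.6 | 0.87 | 1.00 | 1.00 |

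In the second row the score creates a bias that was hardly present before adjustment. In the third row both conditions affect prescribing equally and the bias vanishes. Over a grid of the full ranges the score-adjusted ratio runs from about 0.87 to 1.14, with the score entered as linear or as categories. Some 47% to 52% of scenarios, depending on the grid spacing, lie within 3% of 1.00.

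A second set of assumptions (35% on varenicline, prior respiratory disease in 15–20% against 10–12%, hazard ratio 3–10, three other pooled conditions) gives 0.80 to 1.03.

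**Illustration: absent reading.** With no term for the history, the ratio is [1 + p₁(h − 1)] / [1 + p₀(h − 1)]. With p₁ = 10% on varenicline, p₀ = 15% on nicotine replacement and h = 5, this is 1.4/1.6 = 0.88. The same inputs with the history pooled among three other, balanced conditions give 0.93; with its own term, 1.00.

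**Against the study's precision.** Power calculations reports 1374 patients with a respiratory admission within 2 years in the previous sample of 110 000. Adding the expected 72 000 gives 1374 × 182/110 = 2273. At an assumed 30% varenicline share:

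- SE(log HR) = √[1/(0.3 × 2273) + 1/(0.7 × 2273)] = 0.046
- 95% half-width = 1.96 × 0.046 = 0.09 on the log scale.

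Shifting a normal statistic by log(bias)/SE gives the chance of a nominally significant result under the null, which should be 5%:

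| Bias | Full cohort | 1:1 matched |
|---|---|---|
| 0.93 | 35% | 27% |
| 1.06 | 25% | 19% |
| 1.09 | 47% | 36% |

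The matched column uses √[2/(0.3 × 2273)] = 0.054. Neither SE includes clustering by practice, which the plan will account for; larger SEs would lower these rates.

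**The case against.** The strongest reply is that the article does not say illness enters as one number. The wording could mean a summed score, categories of it, or illnesses identified with the index's definitions, and a separate committee protocol that is not shown may settle the coding. This stands in part. A score is the likelier reading, but it is a reading. The missing separate term for lung or heart history does not depend on it: the list names the covariates and these are not among them.

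A reader might infer more, and the documents do not support it:

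- *That the index gives lung or heart disease the same weight as diabetes or arthritis, or that their diagnoses are extracted and then discarded.* The article lists neither the components nor the weights.
- *That confounding certainly remains.* No figure shows that prescribing depends differently on these conditions.
- *That the previous mortality results prove it.* The adjusted hazard ratio there moved little ("0.43 (95% CI 0.35 to 0.53); after controlling for possible confounders this became 0.49 (95% CI 0.40 to 0.61"), while the instrumental variable risk difference was 0.7 per 1000. That interval, −3.3 to 4.7, is wide; no baseline risk is given to put the two on one scale; and the outcome is all-cause death.

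The illustration is also generous to the remedy. The value of 1.00 with separate terms holds by construction, because the two conditions are the only confounders in it. Age, GP visits, body mass index and deprivation may already absorb part of the bias.

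Two safeguards help only partly. The instrumental variable analysis does not rest on how comorbidity is coded, but an interval as wide as the one above cannot expose a modest bias in a hazard ratio. If the word incident in Outcome 4 means that patients with earlier disease are excluded, the problem shrinks there. No such exclusion is stated, and it would not cover admissions or deaths.

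**Conclusion.** The point holds in a conditional form. The plan names no separate term for prior respiratory or cardiovascular disease, and both hazard-ratio analyses use that list for outcomes these conditions probably drive. Residual confounding follows only if drug choice depends on them differently from the illness they are pooled with or, on the absent reading, if drug choice depends on them at all beyond the listed covariates. Size and sign are unknown: about 0.87 to 1.14 under a true null over the assumed ranges, often within 3% of 1. At the precision expected here, a bias of 6–9% would be enough to matter. The instrumental variable risk differences are not affected in this way. This is a cheap improvement to a recognised modelling choice, not an error or a contradiction in the plan.

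**What to change.** Under Confounding factors, add separate indicators, defined before the first prescription, for prior respiratory disease and for prior cardiovascular disease (including myocardial infarction and heart failure). Enter diabetes, cancer, arthritis and the other index conditions as separate indicators in place of one summed score. Use them all in the fully adjusted Cox models and in the propensity score model, and report balance on each in the matched sample. The summed score can stay as a descriptive baseline item.

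The cost is a sentence or two of protocol text, a few extra parameters among about 180 000 patients and, if the index does not already cover these conditions, a few more code lists.
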